#### Statistical analyses

The primary end point for the statistical analysis will be the between-groups difference in the calculated prevalence of MetS after at least 24 months of follow-up. The full analysis set (FAS) will include all subjects randomized to the intervention arm who achieve a sustained reduction in cigarette consumption of at least 80% during the follow-up, combined with all subjects randomized into the usual standard of care control group. Two approaches to the primary analysis will be used: (a) unadjusted analysis, based on a direct comparison of the change in prevalence using a Z test, and (b) adjusted analysis, where potential confounders (including age, gender, smoking, and medications for hypertension, hyperlipidemia, or diabetes) will be analyzed to identify factors that may influence the primary outcome. A generalized linear model will be used to adjust for identified confounders. Any difference between the groups will be assessed for statistical significance at a two-sided alpha of 0.05.

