## Abstract

Stopping smoking is crucial for public health and especially for individuals with diabetes. Combustion-free nicotine alternatives like e-cigarettes and heated tobacco products are increasingly being used as substitutes for conventional cigarettes, contributing to the decline in smoking prevalence. However, there is limited information about the long-term health impact of those products in patients with diabetes. This randomized controlled trial aims to investigate whether switching from conventional cigarettes to combustion-free nicotine alternatives will lead to a measurable improvement in cardiovascular risk factors and metabolic parameters over a period of 2 years in smokers with type 2 diabetes. The multicenter study will be conducted in seven sites across four countries. A total of 576 smokers with type 2 diabetes will be randomly assigned (1:2 ratio) to either standard of care with brief cessation advice (Control Arm) or combustion-free nicotine alternatives use (Intervention Arm). The primary end point is the change in the proportion of patients with metabolic syndrome between baseline and the 2-year follow-up. Additionally, the study will analyze the absolute change in the sum of the individual factors of metabolic syndrome at each study time point. Patient recruitment has started in September 2021 and enrollment is expected to be completed by December 2023. Results will be reported in 2026. This study may provide valuable insights into cardiovascular and metabolic health benefits or risks associated with using combustion-free nicotine alternatives for individuals with type 2 diabetes who are seeking alternatives to tobacco cigarette smoking. The study protocol, informed consent forms, and relevant documents were approved by seven ethical review boards. Study results will be disseminated through articles published in high-quality, peer-reviewed journals and presentations at conferences.

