### Objectives and end points

Primary end points: The primary objective of the study is to assess the impact of sustained use of C-F NA on the proportion of patients with metabolic syndrome (MetS) among individuals with T2D. The MetS will be defined by the National Cholesterol Education Program (NCEP) MetS score [23], and the primary end point will be the change in the prevalence of an NCEP MetS score below the diagnostic threshold (< 3) between baseline and the 2-year follow-up. The comparison will be made between patients with T2D in both arms of the study.

Secondary end points: The study will also assess the change in MetS prevalence at 3 months, 6 months, and 1 year as secondary outcomes. All assessments at each time point will be performed in all participants in both arms of the study.

Considering the results of several lifestyle modification interventions, the absolute reduction in MetS prevalence after smoking cessation is expected to be no less than 15% [24–28].

Additionally, the study will analyze the absolute change in the sum of the individual factors of MetS, as defined by NCEP criteria, at each study time point (between and within study groups. Other secondary end points will include changes in each individual factor of MetS and changes in the variables at each study time point (between and within study groups).

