### Statistical considerations

#### Powering and sample size calculation

The sample size calculation is based on assumptions that the expected reduction in MetS prevalence after smoking cessation is 15% [24–28], and the expected baseline prevalence of MetS in T2D is 70% [29–32]. Sample size was calculated on the basis of demonstration of superiority, assuming a normal distribution of the sample [33]. Significance level was set at 5% (*α* = 0.05), with a power of 80% (*β* = 0.20). Based on these assumptions, the minimum number of subjects with analyzable data required is 160 per treatment arm (N). Considering an estimated 50% proportion of subjects in the intervention arm achieving sustained reduction in cigarette consumption of at least 80% for the study duration [34–38], the final number of subjects required in the intervention arm (N2) is set at 320. Taking into consideration the expected 20% withdrawal rate in both arms over 2 years, the total number of subjects recruited in each treatment arm is increased by this amount. Thus, the total number of subjects for both arms is set at 576.

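### The primary end point is given both as change in MetS prevalence from baseline and as prevalence at 24 months; the 160 per arm was derived only for the second

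*Protocol article*

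**What the plan says.** The Protocol article describes the primary end point in four places.

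- Abstract: "The primary end point is the change in the proportion of patients with metabolic syndrome between baseline and the 2-year follow-up".
- Objectives and end points: "the primary end point will be the change in the prevalence of an NCEP MetS score below the diagnostic threshold", from baseline to the 2-year follow-up. This counts patients without MetS, so it mirrors the Abstract with the sign reversed.
- Statistical analyses, first sentence: "the between-groups difference in the calculated prevalence of MetS after at least 24 months of follow-up". No baseline value enters.
- Statistical analyses, analysis (a): "unadjusted analysis, based on a direct comparison of the change in prevalence using a Z test".

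Analysis (b) is described by "A generalized linear model will be used to adjust for identified confounders". The form of its outcome is not stated, and baseline MetS status is not among the example confounders listed.

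Powering and sample size calculation assumes 70% prevalence at baseline and a 15% reduction, which Objectives and end points calls absolute. With 80% power this gives 160 analysable patients per arm. No variance of change and no within-patient correlation appears.

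**The concern.** Three statements make the primary variable a change from baseline and one makes it a prevalence at follow-up. The Statistical analyses section contains both. A condensed article may leave detail to an analysis plan, but here it states two different primary variables.

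Two things are at stake. First, in an open-label trial, an end point with two definitions leaves room to choose between them once the data are known. Second, the stated 80% power was worked out for one definition and need not hold for the other.

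The analysis set makes this more pressing. It combines all controls with only those intervention patients who sustain a reduction in cigarettes of at least 80%. Randomization does not guarantee that this selected subgroup matches the controls in baseline MetS prevalence.

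**Working it through.** **Inputs from the article.** Prevalence 70%; absolute reduction 15 points, hence 55%; power 80%; "Significance level was set at 5"%, which Statistical analyses makes two-sided ("statistical significance at a two-sided alpha of 0.05"); 160 analysable per arm; 20% withdrawal. **Assumed, because the article does not give it:** rho, the within-patient correlation of MetS status between baseline and 24 months.

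**1. Reproducing the plan's figure.** Two independent proportions at one time point, unpooled variance:

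n = (1.960 + 0.842)² × [0.70×0.30 + 0.55×0.45] / 0.15² = 7.849 × 0.4575 / 0.0225 = 159.6, so 160 per arm.

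Doubling the intervention arm and adding 20% gives (160 + 320) × 1.2 = 576. Both figures match. The 160 belongs to the 24-month prevalence version.

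**2. How the two estimates relate.** Difference in change = difference at 24 months − difference at baseline. They agree only when the observed baseline difference is zero. By chance alone, with 160 per group at 70%, the standard error of that baseline difference is √(2 × 0.21 / 160) = 0.051, or about 5 points against a planned effect of 15. Selection of the intervention group can add a systematic part.

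**3. Power of the change version at 160 per arm.** Control stays at 70%; intervention goes from 70% to 55%. With paired variance:

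- control: 0.42 − 2·rho·0.21
- intervention: 0.4575 − 2·rho·√(0.21 × 0.2475) = 0.4575 − 0.456·rho
- SE = √(sum / 160); power = Φ(0.15/SE − 1.96)

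| rho (assumed) | Sum of variances | Power at 160 per arm | n per arm for 80% |
|---|---|---|---|
| 0.2 | 0.702 | 62% | 245 |
| 0.3 | 0.615 | 68% | 215 |
| 0.4 | 0.527 | 74% | 184 |
| 0.5 | 0.440 | 82% | 154 |
| 0.6 | 0.352 | 89% | 123 |

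Break-even: the sum must equal 160 × 0.0225 / 7.849 = 0.4587, so rho = (0.8775 − 0.4587) / 0.876 ≈ 0.48. The largest rho possible for 70% to 55% is about 0.72.

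**4. What an open choice costs.** Suppose there is full randomization, no true effect and a correct variance for each version. The two test statistics then correlate at √((1 − rho)/2), which is 0.59 at rho 0.3 and 0.50 at rho 0.5. Claiming success if either is significant raises the two-sided error from 5% to about 9%. Under the planned effect the two versions give opposite verdicts in about 25% of trials at rho 0.3 and 21% at rho 0.5.

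**5. The 24-month version with baseline MetS as a covariate.** Using the approximate variance 0.4575 × (1 − rho²), power at 160 per arm is 80%, 82%, 84%, 86%, 90% and 94% at rho 0, 0.2, 0.3, 0.4, 0.5 and 0.6. At each of these values it is at least as high as the unadjusted 24-month comparison (80%) and higher than the change version.

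**The case against.** The strongest reply is that the intention is clear. Most of the statements say change, and under full randomization both versions estimate the same between-arm difference in expectation. The second part is correct for the randomized arms, but the analysis set is not the randomized arms, and any single trial still yields two different estimates.

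Three stronger readings may tempt a reader, and the article supports none of them.

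- *The Z test uses the wrong standard error.* The article plans a "direct comparison of the change in prevalence using a Z test" and says nothing about its variance. A Z test on within-patient change is valid with the paired variance, and that detail may sit in an analysis plan that is not shown. No error is demonstrated.
- *The trial is underpowered.* Power for the change version falls on both sides of 80%. The MetS definition counts treatment for hypertension, high triglycerides or low HDL as meeting a feature, which makes persistent status, and so a higher rho, plausible. Neither direction can be claimed.
- *The follow-up wording conflicts with the visit window.* V5 is at day 720 ± 7 and the schedule counts 30-day months. V5 is plainly the intended visit, so this is a matter of wording only.

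It is also fair to say that baseline adjustment is a preference. Either definition, stated consistently, would remove the contradiction.

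**Conclusion.** The contradiction stands on the text alone: two incompatible primary end points, both present within one section. The sample size is arithmetically sound for 24-month prevalence and was not derived for change. For change, the stated 80% holds only if the within-patient correlation is about 0.48 or more. Over assumed correlations of 0.2 to 0.6, power is 62% to 89%, so it is not assured but may be met or exceeded.

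These powers assume 160 analysable patients in each group, a stable 70% in controls, a fall to 55% in the intervention group, and the normal approximation. The 9% error rate and the 21% to 25% discordance further assume full randomization. How far selection of the intervention group shifts the two estimates apart cannot be sized from the article.

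**What to change.** State one primary end point in the Abstract, Objectives and end points, and Statistical analyses. Preferably this is MetS present (at least 3 of the 5 features) at V5, compared between arms in the generalized linear model already planned, with baseline MetS status as a covariate. Reword analysis (a) to match, and use presence of MetS, not its absence, throughout. This fits the existing 160 per arm and uses assessments already scheduled at V1 and V5 in Tables 1 and 2. Adjusting for baseline MetS deals with imbalance in that variable only; it does not undo the selection in the analysis set.

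If change is kept, state that the Z test uses the within-patient variance, give the assumed correlation with its basis, and restate the power.

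Cost: a protocol amendment to the end point wording, with ethics review if the chief investigator judges it substantial. Recruitment began in September 2021, so the amendment should be made and dated before outcome data are examined by arm. No new data are needed.

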## Discussion

Smoking cessation is a priority for patients with T2D and the use of C-F NA has grown exponentially in the past decade. However, there is limited knowledge regarding the overall health impact of C-F NA like e-cigarettes and HTPs on individuals with T2D who smoke. The DiaSmokeFree study will be the first trial to address this knowledge gap. The study has been specifically designed to tests the hypothesis that avoiding exposure to cigarette smoke toxicants by substituting tobacco cigarettes for C-F NA may lead to measurable amelioration in cardiovascular risk factors and metabolic parameters, compared to individuals who continue smoking tobacco cigarettes.

Although it is generally desirable, and in particular for individuals with T2D who smoke to stop any form of tobacco consumption, devices that deliver nicotine without combustion (i.e., C-F NA) are de facto replacing tobacco cigarettes among smokers worldwide [39–44]. Compared with tobacco cigarettes, they offer substantial reduction in exposure to toxic chemical emissions [45–49]. For this reason, they are proposed for harm reduction from cigarette smoke and for smoking cessation [18, 21, 50, 51]. However, C-F NA are not risk free, and they might have adverse health effects not yet identified.

DiaSmokeFree's study design was based on the idea that C-F NA are marketed as substitutes for tobacco cigarettes and that the reference product would be participants’ own brand tobacco cigarettes. The study duration of 24 months allows for observation of changes in the primary end point, and the randomized design ensures high-quality data by equalizing variation in smoking history and other variables between the study arms. Additionally, the welfare of participants is emphasized throughout the study with regular reminders to quit smoking and access to free smoking cessation programs.

Several of the parameters measured in this study are associated with the development of cardiovascular diseases (e.g., hypertension, elevated blood cholesterol, and BMI > 25), and some of these parameters have been shown to improve relatively quickly after smoking cessation [34, 35]. Therefore, the profile of these changes after switching to C-F NA may provide valuable insight into the overall potential of these products to reduce the overall cardiovascular risk.

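### The primary analysis set keeps only intervention patients who sustain an 80% cut in smoking but keeps every control, so randomisation does not protect the primary comparison and the 5% error rate is not guaranteed

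*Protocol article*

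**What the plan says.** Under Statistical analyses, the protocol article says of the full analysis set that it is to "include all subjects randomized to the intervention arm who achieve a sustained reduction in cigarette consumption of at least 80% during the follow-up". Those patients are then "combined with all subjects randomized into the usual standard of care control group", with no matching condition on the control side. The primary comparison is to be made in two ways. The first is an "unadjusted analysis, based on a direct comparison of the change in prevalence using a Z test". The second is a generalized linear model adjusting for confounders identified from a list that includes age, gender, smoking, and blood-pressure, lipid and diabetes medication. Differences are to be "assessed for statistical significance at a two-sided alpha of 0.05". No other analysis set is named.

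The restriction is deliberate. Study design, Powering and sample size calculation, and the Discussion all derive the 1:2 allocation from the expectation that only 50% of the intervention arm will reach the 80% reduction.

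Two other statements point to a comparison of the arms as randomised. Objectives and end points says "The comparison will be made between patients with T2D in both arms of the study". The Discussion says "the randomized design ensures high-quality data by equalizing variation in smoking history and other variables between the study arms".

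Study design also lists accepting the advice to stop smoking completely among the possible reasons for premature withdrawal, without limiting this to one arm.

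**The concern.** Membership of the set depends, in one arm only, on what a patient does after randomisation. Patients who hold an 80% reduction for two years probably differ from those who do not in motivation, diet, attendance and use of medication, all of which can affect MetS. The control arm has the same mix of people, but all of them stay in the set. The comparison is therefore between a selected half of one arm and the whole of the other.

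A significant primary result could then reflect who manages to switch, and not what switching does. The name 'full analysis set' makes this hard to see, because readers will take it to mean nearly everyone randomised.

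**Working it through.** **1. The plan's own figure.** Inputs from Powering and sample size calculation: 70% MetS, a 15-point reduction (to 55%), α = 0.05 (two-sided, per Statistical analyses), power 80%. With unpooled variance:

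n = (0.70×0.30 + 0.55×0.45) × (1.960 + 0.842)² / 0.15² = 159.6, so 160 per group, as stated.

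Then 160/0.5 = 320 for the intervention arm. Adding 20% gives 192 + 384 = 576, as stated. The planned numbers reproduce.

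**2. Size of the groups actually compared.** After 20% loss, controls are 192×0.8 = 153.6. The intervention arm is 384×0.8 = 307.2, of whom half qualify: 153.6. So about 154 intervention patients who complete follow-up are left out.

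**3. False rejection when there is no effect.** Assume 70% MetS overall in both arms, half the intervention arm adherent, and a gap g in 24-month prevalence between adherers and non-adherers that has nothing to do with the product. Adherers then have prevalence 0.70 − g/2. The article gives no figure for g, so it is an assumption. For a benefit:

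P = Φ[(g/2 − 1.96×SE₀)/SE₁], with SE₀ pooled and SE₁ unpooled.

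For g = 10 points, SE₀ = √(0.675×0.325×2/153.6) = 0.0534 and SE₁ = √((0.21 + 0.2275)/153.6) = 0.0534. P = Φ(−1.026) = 15.3%, and 15.4% with the opposite tail.

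| Gap, adherers to non-adherers | Adherers below controls | Two-sided false rejection, 153.6 per group |
|---|---|---|
| 0 | 0 | 5.0% |
| 5 points | 2.5 points | 7.6% |
| 10 points | 5 points | 15.4% |
| 15 points | 7.5 points | 28.4% |
| 20 points | 10 points | 45.1% |

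At 160 per group the 10- and 20-point rows are 15.9% and 46.6%. A simulation of 200,000 trials, with 160 controls and 320 intervention patients, gave 16.0% and 46.8%. In the same simulation, comparing all randomised patients kept the rate at 5.0–5.1% for every gap tried (0, 10, 20 and 30 points).

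**4. Power of the all-randomised comparison.** If the 15-point effect occurs only in the adherent 50%, the arm-level difference is 0.5×15 = 7.5 points (70% vs 62.5%). At 153.6 vs 307.2, SE₀ = √(0.65×0.35×(1/153.6 + 1/307.2)) = 0.0471 and SE₁ = √(0.21/153.6 + 0.2344/307.2) = 0.0462. Power = Φ[(0.075 − 1.96×0.0471)/0.0462] = 35.3%. At 160 vs 320 it is 36.6%.

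For 80% power at 1:2, 471 + 942 = 1,413 analysable patients would be needed. If non-adherers also gained 2.5, 5 or 7.5 points (assumed), power at 153.6 vs 307.2 would be 45%, 56% or 66%. If every intervention patient gained 15 points it would be 88%.

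**The case against.** The plan can be defended on several grounds.

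- **The objective concerns sustained use.** That explains the interest in adherers, but it does not make adherers against all controls a valid estimate of the effect in adherers. The controls who would have adhered are not identified.
- **There is an adjusted model.** It deals only with measured confounders. Motivation and diet are not among those listed. Smoking, if taken after baseline, is the selection variable itself. Treatment for hypertension, high triglycerides or low HDL also counts towards MetS in the footnotes to Tables 1 and 2. The model helps but does not restore randomisation.
- **The Z test is described as a test of change.** This largely stands. A stable gap already present at baseline would mostly cancel, leaving only diverging trajectories. The same section also describes the end point as prevalence after at least 24 months, so the text leaves both readings open.
- **The illustrative gaps are large.** This also stands. The 45% figure needs a 20-point gap between adherers and non-adherers, which exceeds the 15-point benefit the plan expects from cessation.

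Some stronger readings are tempting but not supported. A reader might infer that control quitters all remain in the comparison while the intervention arm is filtered. The set does nominally include all randomised controls, but the withdrawal provision in Study design means that those who quit may have no 24-month data. Nor are the statements on both arms and on randomisation errors in themselves: they are true of the arms as randomised, and only the analysis set departs from them. Selecting on cigarette reduction although the objective speaks of product use is at most a weak mismatch, since Methods and Discussion frame the hypothesis as avoiding smoke exposure.

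**Conclusion.** The point stands. The set is fixed in the protocol's own words, so an unseen analysis plan does not explain it as an omission. The primary comparison is not protected by randomisation, and neither planned approach repairs that.

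A reader might go further and conclude that the 5% error rate is certainly broken, or that the bias favours the intervention. The article gives neither a size nor a direction for the difference between adherers and non-adherers, so the supportable statement is that 5% is not guaranteed. The rates of about 15% and 45% rest on assumed gaps of 10 and 20 points in the adherers' favour, half of the arm adherent, and follow-up prevalence as the quantity tested.

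Correcting the set exposes a second consequence. On the plan's own assumptions, with benefit confined to adherers, the randomised comparison has about 35–37% power. That is no reason to keep a non-randomised primary comparison, but it has to be disclosed.

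**What to change.** 1. Define the full analysis set as all randomised patients analysed in the arm assigned, and make that comparison primary. Relabel the present set a non-randomised responder set, supportive only.
2. Reconcile this with the withdrawal provisions in Study design. State how patients who stop smoking or are otherwise withdrawn enter the primary analysis: their week-104 (V5) data where available, otherwise a named missing-data method. A scheduled V5 is not an observed one, and the plan expects 20% withdrawal, so rewording the set is not enough on its own.
3. If an effect in those who switch is wanted, add a complier-average causal effect as supportive: the between-arm difference in MetS divided by the between-arm difference in the proportion reaching the 80% reduction. State its exclusion restriction and why it is doubtful. Patients who cut down by less than 80% may also benefit. Arm B also has 19 scheduled contacts against 6 in Arm A (Tables 1 and 2), which in addition means that sustained reduction is not checked equally often in the two arms.
4. Restate the power for the all-randomised comparison, and revisit the sample size or the target effect openly.

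Items 1 and 3 cost wording. Item 2 may require follow-up of patients who would otherwise be lost. Item 4 is the real cost: 80% power would need about 1,413 analysable patients on the plan's assumptions, and the article expected enrolment to close in December 2023. If the trial cannot grow, the primary result should be reported with its confidence interval and the lower power acknowledged.
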